## Background and rationale

### Diabetes burden of disease

Cardiovascular disease reduced in most European countries during the last 2 decades (Nichols 2013) although large differences exist between migrants and host populations (Pacelli 2016). In Europe, type 2 diabetes and hypertension among refugee and migrant populations were found highly prevalent and often undiagnosed and uncontrolled leading to a higher risk of CVDs.

Hypertension is especially prevalent among migrants from the African region ([name], Reboldi et al. 2016) who often experience obstacles in accessing medical care and low levels of awareness and control (Agyemang 2018). Type 2 diabetes is highly prevalent in all migrant groups living in Europe. Compared with the host populations, the odds for type 2 diabetes is 3.7 for South Asian, 2.7 for Middle Eastern and North Africans, 2.6 for Sub-Saharan Africans, 2.3 for Western Pacific, and 1.3 for Central Americans (Meeks 2016). Studies on South Asian immigrants with diabetes in Italy (Campostrini 2019) also showed that they have more difficulties in reaching glycaemic control. It is not clear if this is due to genetic background, diet, and lifestyle, or to compliance with therapy. Sociocultural factors (cultural beliefs and traditions) affect self-management, dietary habits, medication adherence, and are often causes of scepticism about the benefits of medication (Beune 2019; Alzubaidi 2015).

Notwithstanding these findings, the recent experience of data collection for the WHO Europe Region highlighted the lack of structured data collection systems about these aspects (WHO 2022). In particular, data available in Italy mostly refer to population studies conducted at a local or regional level. (Fedeli 2018; [name] 2021; [name], Calabrese et al. 2017; [name], Castellani et al. 2017)

### Immigrant communities and health promotion

In high-income countries, lifestyle intervention trials resulted in significant improvement in diabetes incidence and glycaemic outcomes. (Hopper 2011; Schellenberg 2013). Nevertheless, interventions developed to improve diet, physical activity and compliance to therapy in immigrant hard-to-reach populations, showed variable effectiveness depending on the context and type of intervention ([name], Galanti et al. 2016). No trials were conducted among immigrant communities in Italy where the close interaction between social and health problems finds a crucial point in the immigrant population not registered in the Regional Health System. The current system in Italy provides that these subjects can be included in the process of care of the Regional Health System by issuing an STP code ("Straniero Temporaneamente Presente"). In this way, the subject can be assisted in relation to the diagnosed problems. However, this requires recognition and diagnosis of the condition that is usually carried out in emergency conditions (during hospitalization for myocardial infarction or stroke) due to barriers in accessing primary care services. In this context, diagnosing high-risk but long-term asymptomatic diseases such as diabetes mellitus or hypertension became more difficult, with a negative impact on primary and

secondary prevention opportunities, and consequently on the burden of diseases in these population subgroups.

The impact of context e minority-specific factors on the effectiveness of prevention strategies highlighted the importance of involving communities in defining health promotion interventions. The co-creation process includes the final users together with other stakeholders to assess health priorities and to define the best strategies to reach individual health aims, removing informal barriers and supporting cultural adaption, thus, finally, reducing inequalities. (Janamian 2016; Leask 2019)

#### The “Cardio-metabolic diseases in immigrants and ethnic minorities: from epidemiology to new prevention strategies.” project

The availability of reliable and routinely collected data on chronic diseases in immigrant populations, the reaching of minorities not registered in the Regional Health System, and evidence-based lifestyle preventive interventions effective among different minorities may contribute to reducing the burden of chronic diseases on the National Health System.

To face this challenge, four research centres located in four different Italian Regions joined a research-intervention project founded by the Italian Ministry of Health within the Piano Nazionale di Ripresa e Resilienza (PNRR) funding program.

Within the first aim of the project, the National Institute for Health, Migration and Poverty (INMP) with the collaboration of the Italian Regions will explore the feasibility of an integrated data collection from the health systems of four regions on chronic disease indicators among immigrant population.

The second aim is focused on the strategies supporting the emergence of the unregistered populations, which remains an unexplored point in Italy as in many areas of Europe. (Woodward 2014)

Finally, the third aim concerns the co-creation of a culture-sensitive intervention to promote healthy diet, and physical activity, and to improve compliance to therapies in immigrants with type 2 diabetes and assess its effectiveness in different minorities at a multicentre level.

## **Study aims**

### **Primary aim**

The aim of the study is to evaluate the efficacy of the co-created, culture-sensitive intervention to promote healthy diet, physical activity, and to improve compliance to therapeutic protocols in immigrants with type 2 diabetes.

The evaluation concerns the efficacy of the intervention in the change of glycated haemoglobin 12 months after recruitment.

## **Secondary aims**

Secondary objectives are:

- Description of changes in:
  - anthropometric measures (BMI, waist circumference)
  - dietary habits
  - physical activity habits
  - lipid profile
  - compliance with individual therapeutic protocols

## **Study design**

The study is a multicentre randomized controlled open trial. The study design is reported in Figure 1.

Immigrants with type 2 diabetes registered at the Italian Regional Health Service or provided with STP code will be recruited.

Across the four recruiting centres, at least four different immigrant communities will be involved.

Endocrinology and Diabetology physicians at Diabetes clinics of both the National Health Service and non-governmental organizations (NGO) will do the recruitment.

Eligible immigrants who accept to participate will sign the consent during routine visits at Diabetes clinics and will be randomized to the control or intervention group.

The intervention group will receive a co-created culture-tailored intervention of health promotion aimed to increase healthy diet, physical activity and compliance with treatment protocols for diabetes.

The control group will receive the health promotion activities routinely performed by Diabetes clinics at the recruiting centres.

The enrolment phase will last 4 months.

The intervention will last at least 3 months.

Follow-up visits will be performed 12 months after recruitment.

The study period will be between 01/01/2023 and 31/12/2025, compatibly with the trend of the COVID-19 emergency.

Questionnaires about diet and physical activity will be collected at baseline and 12-month visits, as well as anthropometric measures.

Blood and urine samples will be collected at baseline and at 12 months to measure glycated haemoglobin and other biomarkers.

[figure not shown]

Figure 1. DiabEthic study design.

### Study population (addendum for operational protocol)

The study will be performed within outpatients and inpatients' Diabetes clinics of the four Italian recruiting centres: Azienda Ospedaliero-Universitaria Careggi (Florence), Istituto Nazionale salute, Migrazioni e Povertà (INMP, Rome); Istituto in tecnologie avanzate e modelli assistenziali in oncologia-AUSL Reggio Emilia; Azienda Ospedaliero Universitaria Mater Domini (Catanzaro).

In each centre immigrants attending routine visits will be assessed for eligibility and, when appropriate, informed of the study and asked to participate. During the enrollment phase, cultural mediators will be involved if needed (subjects who do not speak or understand the Italian language will not be excluded). Due to the different ethnic compositions of the populations living in each centre, different minorities will be involved.

Intervention, control and follow-up will be performed within each centre.

According to the power analysis, at least 200 patients should be recruited overall.

### Eligibility criteria

#### Inclusion criteria

Eligibility criteria include:

- Immigrant status: Self-identification of being born in High migration pressure countries from parents born in High migration pressure countries (Carletti 2009);
- Age  $\geq 18$  years
- Type 2 diabetes newly diagnosed or with HbsA1c  $> 8\%$  in the last assessment within 24 months before the visit

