#### **Exclusion criteria (addendum for operational protocol)**

Exclusion criteria include:

- Patients who will not provide the informed consent
- Patients aged under 18.
- Patients with HbsA1c  $\leq 8\%$  in the last assessment within 24 months before the visit.
- Severe psychiatric disorders
- Pregnant women
- Critical illness
- Impaired cognitive or physical ability that could make the intervention not feasible, as judged by clinical staff members.

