#### **Study endpoints (addendum for operational protocol)**

##### **Primary endpoint**

The primary endpoint is the change in glycated haemoglobin (HbA1c; mmol/mol) between the recruitment and the 12-month follow-up visit assessed through the collection of fasting blood and urine samples.

The difference between groups of the mean change (and standard deviation) in glycated haemoglobin will be used to assess the effectiveness of the intervention.

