### Sample size

To explore the efficacy of a culturally adapted diabetes education model in improving health literacy and self-care (primary endpoint) in immigrant patients with type 2 diabetes. The intervention is expected to provide a 0.5% higher reduction in the concentration of HbA1c compared to the usual care at a 12-month follow-up, with a positive effect on the risk of CVD events (Selvin 2004; Mitsios 2018). Through a change in health-related behaviours, it is also expected to reduce overweight and increase vegetable intake and physical activity, with a positive impact on future risk of non-communicable diseases and quality of life (GBD 2019 Risk Factors Collaborators 2020). To have a power of 80%, considering an alpha of 0.05 (Islam 2013), in order to detect a minimum significant reduction of 0.5% in the glycated haemoglobin in the intervention group compared to the control group at least 200 participants are needed (considering a SD in both group of 1.3) (Bellary 2008).

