#### **Intervention assignment**

Block randomization (1:1 ratio) will be computerized and conducted in each centre to balance the ethnic composition of the intervention and control groups. Members of the same household, whether identified as cohabitant during the recruitment visit, will be assigned at the same arm.

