#### **Subgroup analysis**

Subgroup analyses will be performed according to weight status, gender, ethnicity, and socioeconomic level.

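### The primary HbA1c comparison pools newly diagnosed patients with patients whose last HbA1c was above 8% in an unadjusted test; putting entry route and baseline HbA1c in the primary model would protect precision at almost no cost

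*Protocol*

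**What the plan says.** Under Inclusion criteria, the Protocol accepts "Type 2 diabetes newly diagnosed or with" HbA1c above 8% at the most recent assessment in the past 24 months. One such value is enough; no duration of poor control and no current treatment is required. Exclusion criteria removes patients whose HbA1c was 8% or lower "in the last assessment within 24 months before the visit", and states no exemption for the newly diagnosed.

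The Primary endpoint is HbA1c change "between the recruitment and the 12-month follow-up visit", and the comparison is fixed in one sentence: "The difference between groups of the mean change (and standard deviation) in glycated haemoglobin will be used to assess the effectiveness of the intervention". The Statistical plan names paired and unpaired tests for this. It also plans linear regression models, with no covariates listed, and multilevel models in which centre is the only named factor.

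The Sample size section applies an SD of 1.3 to both arms. It does not say whether this describes change or level, or whether it allows for a mix of entry routes.

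On allocation, Intervention assignment says "Block randomization (1:1 ratio) will be computerized and conducted in each centre", with the aim of balancing ethnic composition. On subgroups: "Subgroup analyses will be performed according to weight status, gender, ethnicity, and socioeconomic level". Entry route appears in neither place.

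**The concern.** The two routes may well follow different courses over 12 months. A newly diagnosed patient in either arm begins diabetes care at about the time of recruitment. A patient from the other route has already been assessed and found above 8%. Baseline HbA1c need not separate them fully: an untreated patient at 9% and a treated patient at 9% can have different expected values a year later.

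If mean change differs by route, the difference adds to the variance of the pooled change scores. An unadjusted test leaves that variance in the standard error, although route is known at the eligibility check and could be taken out. The stake is a wider confidence interval and lower power in a trial whose stated size leaves no reserve.

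**Working it through.** **Inputs from the Protocol (Sample size, Intervention assignment).** Difference 0.5 HbA1c points, SD 1.3, alpha 0.05 (taken as two-sided, since sidedness is not stated), power 80%, 200 participants, 1:1, so 100 per arm.

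**The plan's own figure.** n per arm = 2 × (1.960 + 0.842)² × 1.3² / 0.5² = 106.1, rounded up to 107, or 214 in total. The stated 200 is not reproduced. At 100 per arm, SE = 1.3 × √(2/100) = 0.184, and power = Φ(0.5/0.184 − 1.96) = 77.6%. This shortfall is a separate matter; here it shows only that there is no slack to absorb extra variance.

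**Assumed inputs.** The documents do not give the newly diagnosed share p or the difference D in mean 12-month change between routes. I take p from 0.1 to 0.5 and D from 0.5 to 2.0 points. The sign of D does not matter, because only D² enters.

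**Reading 1: 1.3 is the SD within each route.** Pooled SD = √(1.3² + p(1−p)D²). For p = 0.3 and D = 1: √(1.69 + 0.21) = 1.378.

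| p | D | Pooled SD | Power, 100 per arm, unadjusted | Total N for 80% |
|---|---|---|---|---|
| 0.1 | 0.5 | 1.309 | 77.1% | 216 |
| 0.1 | 2.0 | 1.432 | 69.5% | 258 |
| 0.3 | 0.5 | 1.320 | 76.4% | 220 |
| 0.3 | 1.0 | 1.378 | 72.7% | 240 |
| 0.3 | 2.0 | 1.591 | 60.4% | 318 |
| 0.5 | 0.5 | 1.324 | 76.1% | 222 |
| 0.5 | 2.0 | 1.640 | 57.8% | 338 |

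With route in the model, the SD returns to about 1.3, power to about 77.6% and N to 214.

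**Reading 2: 1.3 already includes the mix.** Unadjusted power stays at 77.6%. Within-route SD = √(1.3² − p(1−p)D²). For p = 0.3 and D = 1: √(1.69 − 0.21) = 1.22, so adjustment gives power of 82.8% at 100 per arm and an N of 186 for 80%.

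**Chance imbalance is the same variance, not a further cost.** With p = 0.3 and D = 1, the between-arm difference in share has SD √(2 × 0.3 × 0.7/100) = 0.065, or 0.065 HbA1c points. Combined with the within-route SE: √(0.184² + 0.065²) = 0.195. The pooled SD gives the same figure: 1.378 × √(2/100) = 0.195. The unadjusted standard error therefore already carries the imbalance.

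These figures isolate route. Baseline HbA1c in the model may remove further variance, and may also absorb part of the route difference; the documents allow neither to be quantified.

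**The case against.** The strongest reply is that nothing here is invalid. Randomisation within centre gives an unbiased comparison, the documents contain no figure for the effect of route, and at the low end of the range the loss is trivial (77.1% against 77.6%). Even the direction is open. The Inclusion criteria set no HbA1c floor for the newly diagnosed, so some may have little room to fall, while selecting on a value above 8% invites regression to the mean in the other group. If the exclusion at 8% or below also binds the newly diagnosed, the mix is narrower. All of this stands, and it is why the size is given as a range under two readings of the SD.

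Covariates may also be listed in an analysis plan that is not shown. That stands for the regression models: their lack of named covariates is not a defect. It does not change the fact that the Protocol states unpaired tests for the between-arm comparison of change.

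A reader might go further and infer that a large fall on first treatment biases the result, or that the trial mixes new cases with long-standing poor control. The documents support neither. They report no fall by route, one last value above 8% is enough for the second route, and chance imbalance under randomisation is imprecision already in the standard error. A reader might also take the absence of route from the strata and subgroups as an error. It is a trade-off. At about 50 patients per centre, with ethnic balance sought and cohabitants kept in one arm, more strata have a cost. An arm-by-route interaction with 60 against 140 patients has SE 1.3 × √(4/60 + 4/140) = 0.40, so 80% power needs an interaction of about 2.8 × 0.40 = 1.1 points, over twice the target effect.

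**Conclusion.** The point holds as one of efficiency, not validity. Two entry routes feed one unadjusted comparison, and adjusting for a baseline factor already in hand is a better primary method than the stated test.

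Its size depends on two quantities that the documents do not give and on an unstated property of the SD. If 1.3 is within route, unadjusted power at 100 per arm runs from 77.1% down to 57.8% over the assumed range (72.7% at p = 0.3, D = 1), against about 77.6% adjusted. If 1.3 covers the mix, there is no loss against plan, only a gain forgone. Adjustment does not lower expected precision in any meaningful way under either reading, so the recommendation does not depend on settling which is right.

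**What to change.** - In the Statistical plan, make the primary between-arm analysis a multilevel linear model (centre, as already planned) of 12-month HbA1c with arm, baseline HbA1c and entry route (newly diagnosed against established with last HbA1c above 8%), in place of the unadjusted unpaired test.
- In Sample size, state whether the SD of 1.3 covers the mix of routes, and preferably the newly diagnosed share expected.
- Reconcile Inclusion criteria with Exclusion criteria on whether the exclusion at 8% or below applies to newly diagnosed patients.
- Optional: stratify randomisation by route, and report an arm-by-route interaction labelled exploratory, with low power.

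The cost is one extra model term for route and one field recorded at the eligibility check. The model change needs no extra patients or visits and can be made after enrolment has started, provided it is fixed before outcome data are analysed by arm. That timing matters because the Protocol leaves the statistician unblinded.

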#### **Exclusion criteria (addendum for operational protocol)**

Exclusion criteria include:

- Patients who will not provide the informed consent
- Patients aged under 18.
- Patients with HbsA1c  $\leq 8\%$  in the last assessment within 24 months before the visit.
- Severe psychiatric disorders
- Pregnant women
- Critical illness
- Impaired cognitive or physical ability that could make the intervention not feasible, as judged by clinical staff members.

## **Interventions**

#### **Intervention A (addendum for operational protocol)**

The intervention will include key elements of proven efficacy for health promotion combined and adapted to each community through a co-design and co-creation process, involving service providers and end-users.

Stakeholders will include professionals involved in diabetes care and providing services to hard-to-reach populations, immigrants with diabetes (the final user), relevant people of the communities and professionals of the third sector. A combination of different methodologies (focus group, consultations, stakeholder meetings, and qualitative interviews among the others) will be used by each centre to co-create a community-tailored intervention [Leask CF 2019] adapted to the local context of each centre with a different implementation of key elements:

- a) Dietary habit: the key elements will be theoretical dissemination of information on healthy diet (i.e. cookbooks with healthy and easy-to-make recipes), and courses on healthy cooking targeted to family and factory cooks (i.e. how to cook healthy dishes respecting the preferences and the taste of the community of origin, but feasible with ingredients available in the hosting region).
- b) Physical activity: the key elements will be the promotion of organized physical activity compatible with the daily time restrictions of the patients, promotion of non-organized physical activity (i.e. analysing the possibilities of moving home-work on foot or by bicycle and using an opportunity map that shows parks and possibilities for spontaneous physical

activity), theoretical dissemination of information on adapted physical activity (i.e. lectures with sports instructors or healthcare professional with specific expertise). Use of apps to measure physical activity will be considered.

- c) Adherence to treatments: tools favouring compliance and glucose measuring, as well as culture-tailored information material on diabetes and its health implications will be used.

The intervention will last a minimum of 3 months and will include at least one individual counselling (IC), one family session, and at least two group sessions (FS) for dietary and physical activity courses. Mandatory elements for the intervention and a non-exhaustive list of optional elements, as well as, elements that can be modulated in the co-creation phase are reported by topic in Table 1.

Table 1: Mandatory and optional elements of the intervention and elements that can be modulated in the co-creation phase.

| Topic                    | Mandatory elements                                                                                     | Optional elements                                                                                                                                      | Co-creation modular elements                                                                                        |
|--------------------------|--------------------------------------------------------------------------------------------------------|--------------------------------------------------------------------------------------------------------------------------------------------------------|---------------------------------------------------------------------------------------------------------------------|
| Diet              | - culturally tailored cookbooks with healthy and easy-to-make recipes                                  |                                                                                                                                                        | - contents of cookbooks                                                                                             |
|                          | - personalised dietary plan                                                                            |                                                                                                                                                        | - food, recipes to be included
- daily timeline of eating opportunities                                          |
|                          |                                                                                                        | - cooking courses for formal and informal cooks including culturally tailored healthy dishes feasible with ingredients available in the hosting region | - Recipes' to be included
- Provider of the cooking courses
- Target of the cooking courses                   |
| Physical activity | - theoretical dissemination of information on adapted physical activity                                |                                                                                                                                                        | - type of sports or physical activity to be included                                                                |
|                          | - opportunity map including cycle lines, parks, public physical activities facilities with free access |                                                                                                                                                        | - Facilities and other elements of interest to be included in the map
- information of interest on each facility |
|                          |                                                                                                        | - promotion of non-                                                                                                                                    | - solutions based on                                                                                                |

|                                |                                             |                                                           |                                                             |
|--------------------------------|---------------------------------------------|-----------------------------------------------------------|-------------------------------------------------------------|
|                                |                                             | organized physical activity using an opportunity map      | specific needs and barriers to be considered                |
|                                |                                             | - organization of courses on structured physical activity | - methodology of courses delivery and sports to be included |
| Adherence to treatments | - Cultural mediation (2 hours per patients) |                                                           | - Mediators to be involved
- Setting for mediation       |
|                                |                                             | - courses to health professional or informal caregivers   | - content of the courses
- caregivers to be involved     |

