### Recruitment process (addendum for operational protocol)

The recruitment will occur within Diabetes clinics routine visits in each centre.

Consecutive enrolment of potentially eligible patients will be performed over a four-month period. Whether low participation rates will occur, a preliminary eligibility assessment on medical records of Diabetes clinics will be performed, and potentially eligible patient will be actively contacted. Pre-recruitment eligibility criteria assessment from third sector organizations caring for undocumented migrants may also support active recruitment.

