#### **Statistical plan**

Descriptive statistics will be calculated for baseline characteristics. The analysis will be intention-to-treat. Before/after variations of the glycated haemoglobin, lipid profile and renal function biomarkers, and anthropometric measure will be computed and standardized if opportune. Paired and unpaired tests will be used to assess the effects of the intervention and to analyse before/after within-group and between-group differences and changes in glycated haemoglobin. Changes in lifestyle habits (both related to diet and physical activities) will be described in terms of positive or negative changes.

Linear regression models will be used to analyse the variation of anthropometric measures and assessed biomarkers.

Multilevel linear models will be performed taking into account the influence of the centre on intervention efficacy.

We will perform a mediation analysis to understand which part of the changes in outcomes (glycated haemoglobin, lipid profile, and anthropometric measures) is attributable to changes in

physical activity, changes in diet, adherence to therapies, and other direct or unmeasured effects of the intervention.

The statistician will not be blinded to group assignments.

The statistical significance level will be set at 5%, and all analyses will be performed by using Stata 16 or SPSS 28.

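### The eligibility criteria do not exclude patients who help co-create a centre's intervention, so some may be randomised to control after working on its content

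*Protocol*

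**What the plan says.** The Protocol's section on Intervention A has each centre adapt the programme to its communities through focus groups, consultations, meetings and interviews. Besides diabetes-care professionals, the stakeholders are "immigrants with diabetes (the final user), relevant people of the communities and professionals of the third sector". Table 1 leaves recipes, eating times, types of activity and map contents, among other things, to this phase.

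Recruitment takes place in the clinics of the same four centres: "Consecutive enrolment of potentially eligible patients will be performed over a four-month period" (Recruitment process). Under Study population, "Intervention, control and follow-up will be performed within each centre". Inclusion requires immigrant status, age 18 or over, and type 2 diabetes that is newly diagnosed or has a last HbA1c above 8%. No inclusion or exclusion criterion refers to co-creation.

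Intervention assignment describes 1:1 block randomisation within centre. Known cohabitants go to the same arm. That is the only stated barrier between the arms.

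Two components are addressed to third parties. The text of Intervention A lists "courses on healthy cooking targeted to family and factory cooks" among its key elements, while Table 1 makes cooking courses optional and leaves their target open. Table 1 also lists "courses to health professional or informal caregivers" as optional.

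**The concern.** Co-creation and recruitment draw on the same communities at the same centres. The two can also share a channel: third-sector professionals are co-creation stakeholders, and third-sector organisations may support active recruitment. A patient who has discussed recipes, activity options and adherence tools, and is then allocated to usual care, is not a clean control.

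Exposure before randomisation cannot be withdrawn afterwards. If nobody records who took part, it cannot be examined in the analysis either. Benefit received by controls biases the primary intention-to-treat comparison towards no difference, and the sample size contains no allowance for it. Only co-creators in the control arm cause this dilution; those in the intervention arm do not.

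**Working it through.** **Inputs from the Protocol (Sample size, Intervention assignment).** Difference 0.5 percentage points of HbA1c; SD 1.3 in both arms; at least 200 patients, 1:1, so 100 per arm; "To have a power of 80%, considering an alpha of 0.05". Sidedness is not stated, and I take the test as two-sided.

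**Step 1. The plan's own figure.** n per arm = 2(1.960 + 0.842)² × 1.3² / 0.5² = 106.1, rounded up to 107, or 214 in total. A one-sided test gives 84 per arm, 168 in total. Neither gives 200; that is a separate matter and the present point does not depend on it.

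Power at 100 per arm: the standard error is 1.3 × √(2/100) = 0.1838, so power = Φ(0.5/0.1838 − 1.960) = Φ(0.760) = 77.6% (77.2% with the t distribution). This is the baseline.

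**Step 2. Dilution.** Let c be the share of the full effect that the average control receives. Then c = (share of controls who co-created) × (fraction of the effect gained by co-creating). The expected difference is 0.5(1 − c), and power = Φ(0.5(1 − c)/0.1838 − 1.960).

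| c | Difference | Power at 200 | Total N for 80% |
|---|---|---|---|
| 0 | 0.500 | 77.6% | 214 |
| 1.25% | 0.494 | 76.6% | 218 |
| 2.5% | 0.4875 | 75.5% | 224 |
| 5% | 0.475 | 73.4% | 236 |
| 10% | 0.450 | 68.7% | 264 |
| 20% | 0.400 | 58.5% | 332 |

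**Step 3. Which c is plausible.** The Protocol gives no count. Assume 5 to 10 patient co-creators per centre, so 20 to 40 over four centres.

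- All enrol, split evenly, full effect: 10 to 20 of 100 controls, c = 10 to 20%. This is the upper end of the loss for this route under the assumed count.
- All enrol, half the effect: c = 5 to 10%.
- Half enrol, a quarter of the effect: 5 to 10 of 100 controls × 0.25, c = 1.25 to 2.5%. Power falls by 77.6 − 76.6 = 1.0 to 77.6 − 75.5 = 2.1 points.

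**Step 4. Does the household rule help?** It keeps cohabitants together but does not decide which arm they enter. A co-creator allocated to control stays in control, along with any enrolled cohabitants.

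**The case against.** The strongest reply is that the text shows a possibility and no more. Co-creators need only have diabetes. To enter the trial they must also be newly diagnosed or have HbA1c above 8%, come to recruitment during the enrolment phase, and consent. Well-controlled patients may co-create and are ineligible. The readable text does not date co-creation relative to enrolment, and the timeline figures are not shown. Discussing what a programme should contain is also far from receiving it: the intervention lasts at least three months, with individual counselling, a family session, at least two group sessions, a personalised dietary plan and cultural mediation. All of this stands, and it is why the small values of c are more credible than 10 to 20%.

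A reader might go further and infer that clinic staff and factory cooks trained under the programme serve both arms, so that controls are certainly exposed. The documents do not support that. The professional courses are optional, may be given to informal caregivers instead, and are not said to be for the trial clinics' staff. Cooking courses are optional in Table 1 with their target undecided, and nothing places participants of both arms at one workplace. The staff route is the more plausible of the two because both arms are managed in each centre, but it remains an inference. Nor is there support for saying that co-creators are unusually engaged patients.

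Adherence is monitored in both arms through clinical records and attendance registers. These could reveal controls attending sessions, but no record of co-creation is named.

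What the reply does not remove is the eligibility gap. Who may enter is fixed in the protocol, and a later analysis plan could not supply the rule.

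**Conclusion.** The point holds as a gap in the eligibility criteria. Nothing keeps co-creation participants out of the trial or out of its control arm, and the household rule does not cover them. The direction of the resulting bias is known, towards no difference; its size is not.

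Under moderate assumptions (20 to 40 co-creators, half enrolled, a quarter of the effect) the cost is 1 to 2 points of power. At c = 5% it is about 4 points (77.6 − 73.4). Losses of about 9 to 19 points require every assumed co-creator to enrol and every exposed control to gain the full effect. All figures rest on a two-sided test, 100 per arm and no dropout. The case for acting is that the change is cheap and the exposure cannot be reversed; it does not depend on a large expected loss. It does not extend to claiming that staff or factory cooks expose controls.

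**What to change.** Add an exclusion criterion: patients who took part in a centre's co-creation activities are not eligible. Add the converse rule that enrolled participants are not invited into co-creation. Continue enrolment to the stated minimum of 200, so that excluded patients are replaced.

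Replacement matters. If 20 or 40 of 200 patients were lost and not replaced, power at 90 or 80 per arm would be 73.2% or 68.2%, below the 75.5% or 73.4% from keeping all of them at quarter-strength exposure. Since 200 is a minimum, replacement is open to the centres.

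Where a centre cannot spare these patients, record co-creation participation before randomisation and pre-specify a sensitivity analysis without them in both arms. Because the status is then a baseline characteristic, removing them leaves a randomised comparison.

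For the optional courses to formal cooks and health professionals, record any delivery to people who also serve control patients. Deferring these courses is not required: courses for factory cooks are among the elements that the text of Intervention A calls key, and postponing them would change what is tested.

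The cost is a few eligible patients lost from the pool, one eligibility line and a short record at each centre.
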